# Herbal medicine foot bath for the treatment of diabetic peripheral neuropathy: protocol for a randomized, double-blind and controlled trial

**DOI:** 10.1186/s13063-018-2856-4

**Published:** 2018-09-10

**Keywords:** Diabetic peripheral neuropathy, Chinese herbal medicine, External application, Randomized controlled trial, Tangbi Waixi decoction, Diabetic foot

## Abstract

**Background:**

As a common complication of diabetes, the incidence of diabetic peripheral neuropathy (DPN) is 60–70% worldwide. DPN is a major risk factor for diabetic foot, which may lead to foot ulceration and even amputation. The treatment of DPN remains challenging. Our preliminary study demonstrated that the external application of Tangbi Waixi (TW) decoction to the lower extremities relieved clinical symptoms and improved nerve conduction velocity in DPN patients. The aim of this study was to verify the efficacy of TW among DPN patients and evaluate the herb mixture’s safety using rigorous methodological designs.

**Methods/design:**

This study is a multicenter, double-blind, randomized controlled trial. A total of 640 DPN patients will be recruited and randomized to receive a foot bath with either the TW decoction or control drug. Participants will be assessed at baseline and 12 and 24 weeks after treatment. The primary outcome was the change of the Toronto Clinical Scoring System (TCSS). Secondary outcomes were nerve conduction velocity, blood glucose, blood lipids, serum inflammatory cytokines, and the European Quality of Life Five-Dimension Scale (EQ-5D) and TCM symptom scores.

**Discussion:**

This multicenter, prospective, randomized clinical trial will provide valuable data regarding the efficacy and safety of foot bath treatment with TW decoction. Positive results would provide a novel treatment regimen for DPN patients.

**Trial registration:**

Chinese Clinical Trial Registry, ChiCTR-IOR-16009331. Registered on 8 October 2016.

**Electronic supplementary material:**

The online version of this article (10.1186/s13063-018-2856-4) contains supplementary material, which is available to authorized users.

## Background

Statistics from the International Diabetes Federation (IDF) demonstrate that there were approximately 425 million people with diabetes worldwide in 2017; it is estimated that the number will increase to 629 million by 2045 [1]. The prevalence of diabetes and pre-diabetes in China has increased to 11.6% and 50.1%, respectively, due to a high calorie intake, sedentary lifestyle, and other risk factors [2, 3]. Diabetic peripheral neuropathy (DPN) is a common chronic complication of diabetes mellitus, with a lifetime prevalence of approximately 50% [4–6]. The clinical symptoms of DPN include itching, numbness, burning sensation, hyperalgesia, and limb weakness, which have a severe negative influence on patient quality of life [7, 8]. DPN is considered a major risk factor for diabetic foot and secondary diseases such as foot ulceration and even amputation [9]. Currently available clinical options for patients with DPN include the following: etiological removal; neurotrophic drugs; and symptomatic treatment; data from several studies did not support positive efficacy [10–12]. Therefore, it is reasonable to develop an effective, safe, and cost-balanced strategy for these patients.

DPN is a microvascular complication caused by local ischemia and neuropathy. Biopsies have revealed graded structural changes in the nerve microvasculature ranging from mild to severe neuropathy [13]. Neuropathy symptoms are more severe in the lower extremities with poor circulation and rich nerve endings. Therefore, therapies meant to improve the microcirculation might alleviate symptoms of DPN. Unfortunately, the frequent failure of oral or intravenous drug administration is due to insufficient plasma concentration in the distal extremities.

Exploring the therapeutic efficacy of local treatment with complementary or alternative medicine is promising. Herbal foot baths have been developed over thousands of years in China. Foot baths not only improve microcirculation [14, 15], they also promote skin permeability to increase the absorption of drugs, which would efficiently increase the efficient drug concentrations at the lower extremities. In addition, traditional Chinese medicine (TCM) considers DPN as collateral retardation due to blood stasis, which would prevent the flow of Qi and blood from reaching the extremities and thus lead to numbness and pain. Therefore, herbs that actively promote the flow of Qi or disperse blood stasis are usually applied to treat DPN; some herbs have demonstrated efficacy for improving the microcirculation [16]. Several studies demonstrated that herbal foot bath therapy is efficacious for the treatment of DPN. However, these studies were not well-designed and did not provide convincing clinical data to support the application of herbal foot baths [17].

Tangbi Waixi (TW) decoction is composed of seven herbal drugs that can activate the flow of Qi and disperse blood stasis. Our preliminary study demonstrated that foot baths with TW decoction promoted local microcirculation, relieved clinical DPN symptoms, and effectively improved the nerve conduction velocity in DPN patients [18]. However, this preliminary study was limited with a small sample size, single center, and non-double-blind design. Therefore, a multicenter, double-blind, randomized, controlled clinical trial is necessary to further determine the efficacy and safety of TW decoction for DPN treatment. We propose that DPN patients treated with TW foot baths will have more positive clinical outcomes than patients receiving the control drug.

## Methods/design

### Study design

The protocol was designed according to Standard Protocol Items: Recommendations for Interventional Trials (SPIRIT) 2013. For the SPIRIT 2013 Checklist, see Additional file 1. This trial was registered at the Chinese Clinical Trial Registry (ChiCTR-IOR-16009331) and any significant protocol changes were revised accordingly. The prospective trial was designed following the principles of multicenter, double-blinded, and was controlled at a randomization of 1:1. The aim was to evaluate the therapeutic efficacy and safety of TW foot baths for DPN treatment. Patients who agree to participate in the study will be asked to provide written informed consent. Patients will be randomly allocated to either the TW experimental group or the control group after attending an educational session related to the clinical study. Patients will receive a foot bath for half an hour once a day (daytime and night are both acceptable) for two weeks and then stop for two weeks; this cycle constitutes a therapeutic course. All patients will be required to visit their clinicians every two weeks to be evaluated. If their Toronto Clinical Scoring System (TCSS) scores are < 6 points, the foot baths will be terminated and the patients will be followed up. If the TCSS scores are > 6 points, patients will receive a total of three therapeutic courses and then be followed up. All patients will be followed for three months after treatment. During the follow-up period, patients will be required to stop the foot baths and visit their clinicians monthly. Patients who drop out due to side effects or personal reasons will be also followed up. The flow chart of the trial is outlined in Fig. 1.

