### Study objectives

The primary objective of this study is to determine the efficacy of TW decoction for improving DPN symptoms, as assessed by TCSS, at the end of treatment and the follow-up period. Secondary objectives include comparison of the side effects experienced in each group over the study period, assessment of nerve conduction velocity between groups at the end of 12 weeks and the follow-up period, and comparison of TCM symptom scores between groups at the end of 12 weeks and the follow-up period. The TCM symptom score will be calculated using the TCM symptoms scoring sheet, which originated from the guiding principles of clinical research on new TCM drugs [19]. Additional secondary objectives will be a comparison of scores calculated by the European Quality of Life Five-Dimension Scale (EQ5D) between groups at the end of 12 weeks and the follow-up period [20, 21] and testing the suitability and feasibility of the proposed outcome measures for the entire clinical trial.

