### Secondary outcome measures

#### Nerve conduction velocity

All patients will be examined by electromyography at baseline, at the end of the treatment, and at completion of follow-up. The bilateral motor and sensory nerve conduction velocity of the median and common peroneal nerve will be calculated.

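### The time of the primary TCSS reading is not fixed consistently: treatment ends when TCSS falls below 6, and end of treatment and week 12 coincide only for patients not stopped early

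*Protocol article*

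**What the plan says.** All statements are in the protocol article.

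- **Study design, stopping.** Patients are seen every two weeks. For a score below 6 "points, the foot baths will be terminated and the patients will be followed up". For a score above 6 "points, patients will receive a total of three therapeutic courses and then be followed up". A course is two weeks of baths and two weeks without.
- **Study design, follow-up.** "All patients will be followed for three months after treatment".
- **Study objectives, primary.** Efficacy is "as assessed by TCSS, at the end of treatment and the follow-up period", with no week given.
- **Abstract, Methods/design.** "Participants will be assessed at baseline and 12 and 24 weeks after treatment".
- **Study objectives, secondary.** The list includes "assessment of nerve conduction velocity between groups at the end of 12 weeks and the follow-up period".
- **Nerve conduction velocity.** "All patients will be examined by electromyography at baseline, at the end of the treatment, and at completion of follow-up". The blood glucose, lipid and cytokine sections use the same end-of-treatment timing.

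Entry requires TCSS of at least 6 with no limit on severity. The sample size section assumes mean falls of 3.5 points (TW) and 1.5 points (control).

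**The concern.** The primary outcome triggers the end of treatment, and one of the stated timings reads the primary outcome at the end of treatment. On that reading two things follow.

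First, an early stopper's value is the first reading that happened to fall below 6. With measurement error, such a value is on average lower than the patient's true score.

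Second, if TW works, more TW than control patients stop early, so the arms are compared at different average times since randomisation. Patients entering at 6 to 8 can stop after a fall of only 1 to 3 points, less than the mean fall planned for TW.

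The other stated timing, fixed weeks, avoids both problems. But the text does not choose between the two, so sites and the analyst could take different values for the same patient and each be following the protocol.

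**Working it through.** **1. The calendar implied by the text.** Three courses are 3 × (2 + 2) = 12 weeks. Treatment can end at week 2, 4, 6, 8, 10 or 12. Taking three months as about 12 weeks, follow-up ends between week 2 + 12 = 14 and week 12 + 12 = 24.

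| Source | Stop at week 2 | Full 12 weeks |
|---|---|---|
| Study design with primary objective: end of treatment, end of follow-up | weeks 2 and 14 | weeks 12 and 24 |
| Abstract, read as weeks from randomisation | weeks 12 and 24 | weeks 12 and 24 |
| Abstract, read literally as weeks after treatment | weeks 14 and 26 | weeks 24 and 36 |

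Rows 1 and 2 agree only in the right-hand column. Row 3 contradicts the three-month follow-up in both columns. Under row 2, a week-2 stopper needs a week-24 visit that the three-month rule does not provide. Nerve conduction shows the same split between Study objectives (12 weeks) and its own section (end of treatment).

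**2. Size of the effect (illustration).** The documents give no baseline distribution, SD or measurement error. Assumptions:

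- true baseline normal with mean 8, 10 or 12 and SD 3, admitted if the rounded score is 6 to 19 (enrolled means about 9.3, 10.5 and 12.1);
- 12-week fall with mean 3.5 or 1.5 and between-patient SD 2, accruing linearly;
- visit error SD 1.0 or 1.5, scores rounded, stop at the first score below 6;
- 200,000 patients per arm; after a stop the true score stays where it is, or half the gain is lost (50% rebound).

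Ranges below are over the two error SDs; early stopping means before week 12.

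| Enrolled mean | Early stop, TW v control | Mean end-of-treatment week | Difference, end of treatment | Difference, common week 12, no rebound | Same, 50% rebound | Difference, no stopping rule |
|---|---|---|---|---|---|---|
| 9.3 | 50–56% v 31–39% | 8.4–8.9 v 9.4–9.9 | 1.40–1.42 | 1.27–1.30 | 0.93–0.99 | 1.93–1.97 |
| 10.5 | 32–37% v 18–23% | 9.8–10.2 v 10.6–10.9 | 1.67–1.69 | 1.50–1.56 | 1.23–1.29 | 1.96–1.98 |
| 12.1 | 17–21% v 8–11% | 10.9–11.2 v 11.4–11.6 | 1.85–1.88 | 1.73–1.77 | 1.53–1.59 | 1.98–1.99 |

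**3. Within-arm overstatement** (end-of-treatment fall minus week-12 fall, no rebound). Largest: TW, enrolled mean 9.3, error SD 1.5: 3.38 − 2.55 = 0.83. Smallest: control, enrolled mean 12.1, error SD 1.0: 1.50 − 1.40 = 0.10. With true baseline means of 9 to 11 and error SD 0.5 to 1.5 the range is about 0.1 to 0.7.

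**4. Selection alone.** With no true change and error SD 1.5, the mean recorded fall at end of treatment is 0.77 (true mean 8) or 0.41 (true mean 10), against 0.27 or 0.12 at a fixed week 12.

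**5. Type I error.** With equal falls in both arms, 266 per arm and end-of-treatment values, the t-test rejected in 0.050 of 3,000 runs.

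**The case against.** **Fixed weeks are stated.** The Abstract gives 12 and 24 weeks, and the schedule figure (Fig. 3), not shown here, may repeat them. A reader might infer that assessment time definitely differs by patient and arm; the documents do not support that as fact. If week 12 from randomisation applies to all, timing is equal and no first-crossing value is used. What stands is the conflict, because no figure can make both texts true.

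**The change is not capped.** A stopping score can be anything from 0 to 5, so early stopping truncates improvement without setting a ceiling. Entrants at 6 to 8 are only part of the sample.

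**The trial is not biased towards TW.** A reader might infer this from the first-crossing selection. In every scenario the between-arm difference is below its value without stopping, and type I error holds.

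**Loss of power is not shown.** With 266 per arm and a difference of 1.38 (week 12, true baseline mean 9, error SD 1.5), power = Φ(1.38 / (SD × √(2/266)) − 1.96). That is 98% at SD 4 and 89% at SD 5. It is about 61% only at SD 7.1, the value back-solved from the planned size as 2 × √(266/2) / (1.960 + 1.287), which the documents do not state.

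**Exposure differs less than the calendar suggests.** Baths fall in weeks 1–2, 5–6 and 9–10, so a week-10 stopper has had every bath. The linear accrual in the simulation ignores this.

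**Regimen end is a definable contrast.** Comparing treat-until-below-6 regimens at their end is possible, and repeated-measures ANOVA is also planned. But neither tells an analyst which TCSS value of an early stopper is primary.

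**Conclusion.** The point holds as an unreconciled definition of the primary time point. Study design, Study objectives, the Abstract and the nerve conduction section agree only for patients not stopped early. This rests on the text alone and needs no simulation. It is more than detail left to an analysis plan, since the stated timings contradict each other.

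The size is illustrative. Under the assumed inputs, a planned 2-point difference becomes about 1.4 to 1.9 at end of treatment, and about 1.3 to 1.8 at a common week 12 without rebound (about 0.9 to 1.6 with 50% rebound). Within-arm falls are overstated by roughly 0.1 to 0.8 points if read at end of treatment. The effect is largest for a mild population with noisy scoring and small when most patients enter well above 6. The direction was the same throughout: dilution of the between-arm difference, with type I error intact.

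A common week 12 does not restore the 2-point planning difference; it moves somewhat further from it. Its merit is a defined time and no selected reading. Whether the planning falls already reflect a similar stopping rule cannot be judged from the article.

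**What to change.** - State the primary endpoint as TCSS change from baseline to week 12 after randomisation, and the follow-up endpoint at week 24 after randomisation. Measure both in all randomised patients, whether or not baths stopped early.
- Use the same weeks for nerve conduction, blood measures, EQ-5D and TCM symptom score. Correct the Abstract's reference to weeks after treatment.
- Extend the follow-up of early stoppers to week 24.
- Use the week-12 TCSS even when it is the first below 6; excluding it would discard a valid value and conflict with the planned intention-to-treat analysis. Do not substitute an earlier stop-triggering value for it. Time to TCSS below 6 may be reported separately by arm.
- State that the estimate is for the regimen including early stopping and may be smaller than 2 points.

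**Cost.** Amendment wording and some visits. Taking a month as four weeks, monthly follow-up already reaches week 12 for stops at weeks 4 and 8; stops at weeks 2, 6 and 10 need a re-timed or extra visit. All early stoppers need a week-24 visit. Recruitment began in November 2016, so some early stoppers may be past these weeks; how their missing values are handled should be fixed before unblinding.

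The sponsor must reconcile the stopping rule, which leaves a score of exactly 6 uncovered, with the assessment sections. No clinical rule is proposed here.

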**Fig. 1 Fig1:**
[figure not shown]
Flow chart of the clinical study

### Study setting

This multicenter study will be coordinated by Guangdong Provincial Hospital of Chinese Medicine and sponsored by the State Administration of Traditional Chinese Medicine of China. The study will recruit patients from collaborating sites across China, as listed in Table 1. Each research institution will supply similar foot bath equipment that has automatic heating, time setting, and water temperature preservation functions. These conditions will ensure that each patient receives the same foot bath environment at 42 °C lasting for 30 min.

**Table 1 Tab1:** Collaborating institutions for DPN patient recruitment

◆	Eastern China
	- Beijing University of Chinese Medicine Affiliated Dongzhimen Hospital
	- Affiliated Hospital of Liaoning University of Traditional Chinese Medicine
	- Guangdong Provincial Hospital of Chinese Medicine
	- Hainan Provincial Hospital of Traditional Chinese Medicine
◆	Middle China
	- Anhui Provincial Hospital of Traditional Chinese Medicine
	- Liuyang Hospital of Traditional Chinese Medicine
	- Luoyang No. 1 Hospital of Traditional Chinese Medicine
◆	Western China
	- Guizhou Provincial Hospital of Traditional Chinese Medicine

### Study objectives

The primary objective of this study is to determine the efficacy of TW decoction for improving DPN symptoms, as assessed by TCSS, at the end of treatment and the follow-up period. Secondary objectives include comparison of the side effects experienced in each group over the study period, assessment of nerve conduction velocity between groups at the end of 12 weeks and the follow-up period, and comparison of TCM symptom scores between groups at the end of 12 weeks and the follow-up period. The TCM symptom score will be calculated using the TCM symptoms scoring sheet, which originated from the guiding principles of clinical research on new TCM drugs [19]. Additional secondary objectives will be a comparison of scores calculated by the European Quality of Life Five-Dimension Scale (EQ5D) between groups at the end of 12 weeks and the follow-up period [20, 21] and testing the suitability and feasibility of the proposed outcome measures for the entire clinical trial.

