### Sample size

The primary outcome measure of the study is TCSS; hence, the sample size will be calculated based on preliminary TCSS results. We anticipate that TCSS scores will decrease 3.5 points in the TW foot bath group compared with 1.5 points in the control group [30, 31]. Based on a two-tailed type-1 error of 0.05 and a type-2 error of 0.099, we anticipate that 266 patients will need to be recruited for each group. Given the possibility of exclusion or lost follow-ups, an increase of 20% will be required for the sample size; therefore, 320 patients will be enrolled in each group.

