### Statistical analysis

A statistician blinded to the patient allocation for each group will perform all analyses using PASW Statistics 17.0 software. Statistical analysis will be performed on an intention-to-treat (ITT) basis with 95% CI. The ITT analysis will include all randomized patients. All data will be presented as mean ± standard deviation and compared between groups using unpaired Student’s *t*-tests. Comparisons within a group will be performed using analysis of covariance. Count data will be analyzed using chi-square tests. Repeated measure ANOVA will be performed to assess the changes within and between groups over time. Subgroup analyses will be performed according to the treatment periods. *P* < 0.05 will be considered statistically significant.

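### The primary objective names TCSS at two time points without saying whether either or both must succeed, so the type-1 and type-2 errors given for a single comparison cannot both hold

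*Protocol article*

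**What the plan says.** - **Study objectives.** The primary objective is efficacy on symptoms "as assessed by TCSS, at the end of treatment and the follow-up period". No rule links the two time points.
- **Abstract, Methods/design.** The primary outcome is given only as the change in TCSS. On timing: "Participants will be assessed at baseline and 12 and 24 weeks after treatment". Study design adds: "All patients will be followed for three months after treatment". Three four-week courses followed by three months of follow-up fit assessments at about 12 and 24 weeks from the start.
- **Statistical analysis.** "All data will be presented as mean ± standard deviation and compared between groups using unpaired" Student's t-tests. Then: "Repeated measure ANOVA will be performed to assess the changes within and between groups over time". A P value below 0.05 "will be considered statistically significant". No time point or test is put ahead of another.
- **Sample size.** "Based on a two-tailed type-1 error of 0.05" and a type-2 error of 0.099, 266 patients per group are needed for an expected fall of 3.5 points against 1.5. Neither the time point nor the standard deviation is given.

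**The concern.** A trial sized for one comparison at one significance level needs one deciding comparison. Here the objective offers two time points and the analysis section offers two kinds of between-group test, all at the same threshold. A reader of the final report could not tell from the protocol which result was meant to settle the question. If a difference appears at only one time point, both a positive and a negative reading could be defended after the fact. Depending on the reading, either the stated 5% chance of a false positive or the stated 9.9% chance of missing the planned effect is wrong.

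**Working it through.** **1. The plan's own figure.** Inputs from Sample size: difference 3.5 − 1.5 = 2.0, two-sided α = 0.05 (z = 1.960), power 1 − 0.099 = 0.901 (z = 1.287), n = 266 per group. From n = 2·[SD·(1.960 + 1.287)/2.0]², the missing SD back-solves to 2.0 / (3.247 × √(2/266)) = 7.10. So 266 cannot be derived from the stated inputs alone, but it is the size for **one** contrast with an SD of about 7.1. That SD is used below only to price a Bonferroni alternative.

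**2. Two t-tests, one per time point.** Let ρ be the correlation between the two test statistics. The document gives none, so 0 to 0.9 is an assumed range. For bivariate normal statistics:

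- either significant under no effect: 1 − P(|Z₁| < 1.96 and |Z₂| < 1.96)
- both significant under no effect: 0.05 + 0.05 − (either)
- joint power with 0.901 at each time point: Φ₂(1.287, 1.287; ρ)

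| ρ | Type-1, either suffices | Type-1, both required | Joint power, both required |
|---|---|---|---|
| 0 | 0.0975 | 0.0025 | 0.812 |
| 0.3 | 0.0951 | 0.0049 | 0.823 |
| 0.5 | 0.0907 | 0.0093 | 0.834 |
| 0.7 | 0.0835 | 0.0165 | 0.848 |
| 0.9 | 0.0704 | 0.0296 | 0.870 |

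The third column assumes no effect at either time point. If there is an effect at only one of them, the rate under the both-required rule still cannot exceed 0.05.

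**3. Adding the ANOVA tests under the either-suffices reading.** Simulation of 12,000 null trials per setting: 100 per arm, three visits, equal within-patient correlation of 0.3, 0.5, 0.7 or 0.9, t-tests on change from baseline.

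| Counted as success | Chance of at least one P < 0.05 |
|---|---|
| Either t-test | 0.086–0.095 |
| Either t-test or group-by-time | 0.094–0.106 |
| Any of these or the group main effect | 0.141–0.151 |

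The first row is a check. With equal correlation r between visits, two changes from a common baseline correlate (1 − r)/[2(1 − r)] = 0.5, for which step 2 gives 0.0907. The simulation error is about √(0.09 × 0.91/12,000) = 0.003, so the spread is noise. If the t-tests were run on raw visit scores, adding group-by-time would give 0.124–0.127. Change scores are the main case because the abstract defines the outcome as change.

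**4. Alternatives.**
- One deciding comparison, then the other in fixed sequence: type-1 error 0.05 over both, 266 per group unchanged.
- Bonferroni at 0.025 each (z = 2.241): 266 × [(2.241 + 1.287)/3.247]² ≈ 314, or 315 per group by the exact calculation. At 266, power falls to Φ(3.247 − 2.241) = 0.843.

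**The case against.** The strongest reply is that no inflation is written into the document. It nowhere says that any one significant result makes the trial positive, and the objective joins the two time points with "and", which can mean that both are required. On that reading type-1 error is at most 0.05. This stands: a reader might infer that the false-positive rate simply is well above 5%, and the text does not support that as a fact. But the both-required reading does not rescue the plan, because the stated type-2 error then fails.

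Second, a reader might infer that t-tests and ANOVA are both run at each time point and take the 0.14 to 0.15 figure as the size of the problem. The text describes one ANOVA over time. The figure also needs the group main effect to count as success. That effect averages over visits, baseline included where baseline is one of them, so it is not a test of change, and the protocol does not call it an efficacy test.

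Third, this is a condensed article, and test order or multiplicity adjustment may sit in an analysis plan not shown. That is fair: a missing adjustment paragraph is no finding. What remains is what the article itself fixes, namely two time points in the primary objective against a sample size for one comparison. An analysis plan would have to narrow the objective or restate the power.

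Finally, nothing in the sample size section ties its contrast to week 12 or to a baseline-adjusted model, so choosing them is a recommendation, not a correction back to the plan. The DSMB reviews are described for progress and adverse events, so they add nothing to the count.

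**Conclusion.** The concern holds in a conditional form. The type-1 error of 0.05 and type-2 error of 0.099 cannot both apply to a primary objective with two time points:

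- **Either suffices:** type-1 error about 0.07 to 0.0975 for the two t-tests, about 0.09 to 0.10 with group-by-time added, and about 0.14 only with the group main effect as well.
- **Both required:** type-1 error at most 0.05, joint power about 0.81 to 0.87 instead of 0.901.

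These sizes rest on an assumed correlation of 0 to 0.9 between time points, power of 0.901 at each, and t-tests on change scores. The documents do not say which reading is meant, so neither an inflated false-positive rate nor a loss of power can be asserted outright. This is a cheap improvement worth making, not a flaw that invalidates the design.

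**What to change.** Before unblinding, name one primary comparison. An example is the between-group difference in TCSS change at the scheduled 12-week assessment, from one stated model, at two-sided 0.05, with a statement that the sample size calculation refers to it. Adjustment for baseline TCSS is preferable, but it would be new: the protocol assigns analysis of covariance to within-group comparisons. Naming the scheduled visit also helps because foot baths can end early under Study design, so a patient's end of treatment need not fall at week 12.

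Test week 24 only if week 12 is significant, in fixed sequence at the full 0.05. Label the other t-tests and the ANOVA tests supportive. If both time points are meant to be required, say so and restate the power in the sample size section.

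The cost is wording, with 266 per group unchanged under the fixed sequence. The downside is that an effect seen only at week 24 would no longer count as a primary success.

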### Monitoring

This study will be performed in accordance with the approved protocol. An independent Data and Safety Monitoring Board (DSMB) will be formed before the trial start. The DSMB will review the data after 25%, 50%, and 75% enrollment to monitor the study progress and all adverse events (AEs) that may occur.

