### Adverse events

All AEs will be recorded and any serious adverse events (SAEs) will be reported to the Research Ethics Committee (REC) within 24 h. When AEs occur, the study investigators will request that the patient terminate the foot bath and then determine whether this event was related to the investigational formula. The chief investigator may implement urgent safety measures to protect patients from immediate harm. If the AE is related to the investigational formula, it will be termed a side effect. If the side effect is mild and the patient agrees to commence, the foot bath treatment will continue after the symptoms abate. Patients will withdraw from the study if SAEs are observed.

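### As worded, the one between-group safety objective compares only adverse events judged related to the formula, although all adverse events are recorded

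*Protocol article*

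**What the plan says.** The Study design section states a general aim: "The aim was to evaluate the therapeutic efficacy and safety of TW foot baths for DPN treatment". Study objectives turns the safety part into one secondary objective that compares the groups, the "comparison of the side effects experienced in each group over the study period".

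The Adverse events section sets out how events are handled. Collection is complete: "All AEs will be recorded and any serious adverse events (SAEs) will be reported to the Research Ethics Committee (REC) within 24 h". When an AE occurs, the investigators have the patient stop the foot bath and "then determine whether this event was related to the investigational formula". It then fixes the term used in the objective: "If the AE is related to the investigational formula, it will be termed a side effect". No other definition of a side effect appears in the article.

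Two other places touch on AEs. Under Monitoring, the data and safety monitoring board (DSMB) reviews data at 25%, 50% and 75% of enrolment "to monitor the study progress and all adverse events (AEs) that may occur". Under Statistical analysis there is a general rule, "Count data will be analyzed using chi-square tests", which names neither AEs nor SAEs. The listed primary and secondary outcome measures contain no AE endpoint.

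**The concern.** Randomisation supports a comparison of all AEs between the arms without anyone deciding what caused each event. A comparison limited to events judged related depends instead on a case-by-case opinion, given at eight sites, and the article states no criteria for it.

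The reference point for that opinion is also narrow. Relatedness is judged against the formula, not against the foot bath as delivered. The Discussion itself names scalding as a hazard for patients who have lost thermal sensation. An investigator could attribute a scald to the water temperature or the device, and it would then not be a side effect by the protocol's definition.

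SAEs raise the same problem. The Adverse events section has patients withdraw when an SAE is observed, with no condition on cause, yet an SAE judged unrelated is not in the stated comparison. Safety is a declared aim of the trial, so what its one comparative safety objective covers matters.

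**Working it through.** **Step 1: the texts side by side.**

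| Place in the Protocol article | Which events | Compared between arms? |
|---|---|---|
| Study objectives | Side effects | Yes |
| Adverse events, definition | Side effect = AE related to the formula | Supplies the meaning |
| Adverse events, recording | All AEs | No, collection only |
| Monitoring | All AEs | Not stated; described as monitoring |
| Statistical analysis | Count data in general | Chi-square; AEs not named |

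Putting the definition into the objective gives: compare, by group, the AEs judged related to the formula. No other row states a comparison of all AEs or SAEs by arm.

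**Step 2: what this does to power.** The plan has no safety power figure to reproduce. The sample size, 320 per arm, comes from the Sample size section. All AE rates below are assumptions. The formula is the normal approximation for two proportions, two-sided 5%:

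power = Φ[(d − 1.96·SE0) / SE1], where d = p1 − p2, SE0 = √[2·p̄(1 − p̄)/320], p̄ = (p1 + p2)/2, and SE1 = √[(p1(1 − p1) + p2(1 − p2))/320].

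Example, 12% v 5%: d = 0.07, p̄ = 0.085, SE0 = 0.0220, SE1 = 0.0219, so power = Φ[(0.07 − 0.0432)/0.0219] = 0.89.

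*Scenario A: the same share of AEs, one half, is judged related in each arm, so half of the true excess is labelled unrelated.*

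| All AEs | Power | Judged related | Power |
|---|---|---|---|
| 12% v 5% | 0.890 | 6% v 2.5% | 0.593 |
| 10% v 5% | 0.671 | 5% v 2.5% | 0.384 |

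*Scenario B: attribution is accurate, and unrelated events are an independent 20% background in both arms.* The all-AE rate is 1 − (1 − related rate)(1 − 0.20). For 8% related this is 1 − 0.92 × 0.80 = 26.4%; for 2%, 1 − 0.98 × 0.80 = 21.6%; for 10%, 28%; for 5%, 24%.

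| Judged related | Power | All AEs | Power |
|---|---|---|---|
| 8% v 2% | 0.938 | 26.4% v 21.6% | 0.295 |
| 10% v 5% | 0.671 | 28% v 24% | 0.210 |

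In A the restricted comparison is the weaker one; in B it is the stronger. The direction depends on how accurate attribution is and on the background AE rate, and the documents give neither.

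**Step 3: could attribution favour an arm?** The Blinding section keeps investigators, participants and medical staff unaware of assignment, and the Randomization section allocates 1:1 within each site. Differences between sites in how readily events are called related are therefore spread over both arms. What remains is misclassification: real harms labelled unrelated, to an extent that varies by site.

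**The case against.** The strongest case on the other side is that the objective may not use the term in its defined sense. The article uses it loosely elsewhere: as a reason for dropping out (Study design) and for the drawbacks of pain medication (Discussion). In the Adverse events section the definition leads into whether the foot bath may resume; it is not offered as an analysis rule. This has force, and the intention may well have been broader. It does not remove the point, because that definition is the only one given and someone following the text would apply it.

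A second argument is that AE tables are normally left to the full protocol or the analysis plan, neither of which is shown. That is correct, and the absence of an AE table list is no finding. The point here is narrower: the article does state the safety objective and does define its key word, and the combination is too narrow.

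A reader might go further and infer three things that the documents do not support.

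- *That events judged unrelated are lost or will never be compared.* They are recorded, the DSMB sees them, and the chi-square rule is not limited to related events. They are only outside the comparison that is stated.
- *That the restriction necessarily costs power.* Scenario B shows the reverse.
- *That attribution will be biased by arm.* Blinding argues against it. Nor does the article show that the one-tenth herbal content of the control makes attribution harder.

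**Conclusion.** The point holds as a matter of wording. Applying the protocol's own definition, the single stated between-group safety comparison leaves out AEs and SAEs judged unrelated to the formula, although the data to include them are collected.

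Its size cannot be fixed from the documents. Under the assumed rates, power with the restricted comparison runs from 0.38 (against 0.67 for all AEs) to 0.94 (against 0.29). Neither comparison is better in every case, which is a reason to state both in advance. The conclusion rests on reading the objective by the only definition given, and on the article alone; a fuller document may already tabulate all AEs by arm. The matter is modest in weight but worth correcting, because it concerns a declared aim and costs little.

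**What to change.** Reword the safety objective in Study objectives so that it compares, by randomised arm and regardless of causality, the proportion of patients with:

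- any AE;
- any SAE;
- any AE leading to a stop of the foot bath.

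Report AEs judged related, under the existing definition of side effects, alongside these. For the third item, state whether a temporary interruption counts: the Adverse events section has the bath stopped at every AE, so without that statement the item could coincide with the first.

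The cost is a change of wording and a few extra tables. The headline AE percentages will be higher than with related events alone. No new data are needed, and no rule for managing patients changes.
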